## Abstract

**Background:**

Severe soft tissue infections are surgical emergencies typically accompanied by sepsis. Early recognition and management optimizes patient outcomes. Single-centered studies on these infections are limited due to their rare incidence.

**Materials & methods:**

We propose a protocol for the SENSEI (Severe Necrotizing Soft Tissue Infections) study, a multi-centered audit across the United Kingdom to assess current clinical practice for treating severe soft tissue infections in adult and paediatric populations. This will be compared with standards predetermined by the Surviving Sepsis Campaign and Sepsis 6. This audit will follow a trainee collaborative model, where doctors in surgery and ICU are invited to participate by the Reconstructive Surgery Trials Network and Paediatric Critical Care Society Audit Network. Each site will have a local lead, and at least one collaborator each from surgical and intensive care teams. Data collected will include presentation, investigations, and management of severe soft tissue infections.

**Ethics & dissemination:**

As the SENSEI study is an audit and not research, approval is not required from a NHS research ethics committee. Findings of the study will be reported in scientific meetings and peer-reviewed journals.

## Introduction

Severe necrotizing soft tissue infections (SSTIs) are a group of life-threatening infections, with reported mortality rates as high as 40 %.^1^ There are estimated to be 500 new cases every year with 0.4 to 0.53 cases per 100,000 population.^2^^,^^3^ They are surgical emergencies, characterized by rapidly progressive necrosis of subcutaneous tissue, fascia or muscle, accompanied by sepsis. In addition to mortality, SSTIs can have a long-term psychosocial impact on both patients and their families.^4^ Prompt surgical management and broad-spectrum antibiotics are essential for treating SSTIs. Surgery involves complete debridement of infected and necrotic tissue to limit the spread of the infection.^5^^,^^6^ In extensive upper and lower limb infections, this may involve amputation. Early debridement leads to reduced mortality, fewer number of surgical debridements needed, a lower risk of septic shock and multi-organ failure, and a shorter hospital stay.^7^, ^8^, ^9^, ^10^

While early diagnosis and management can minimize mortality and morbidity, early recognition of SSTIs is challenging. Over half of patients are misdiagnosed at the early stages of disease, and the symptomatic triad of pain, erythema and swelling can be mistaken for the more common cellulitis or abscess.^11^ Delayed surgical decision, and unavailability of surgeons and facilities (such as operating theatre space) can further defer treatment.^12^^,^^13^ Interhospital transfer to a facility that can provide surgical debridement is also associated with increased mortality due to SSTIs.^14^ Essentially, delays in any aspect of SSTI management increases mortality but are unavoidable if the infection is recognized too late.

The aim of this study is to evaluate current approaches to managing SSTIs in the UK against “Surviving Sepsis Campaign” (SSC) and Sepsis 6 guidelines, and carry out a national retrospective analysis of SSTI cases including both adult and pediatric patients. Data from this study will be used to inform future research on SSTI treatment.

### Aims

Primary aim:•To audit current practice for SSTIs against SSC and Sepsis 6 guidelines for adults and children.

Secondary aim:•To provide a standardized approach to reporting SSTIs for future audits.•To establish epidemiology of SSTIs in the UK.•To identify key areas for future research.

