## Materials/patients and methods

A national, multi-centered audit of NHS hospitals in England, Wales, Scotland and Northern Ireland will be carried out to achieve the above aims. Data collection will be retrospective to understand how documentation for both SSTIs and sepsis varies between sites, and can inform the methodology for later prospective studies. This study will follow a trainee collaborative model. Trainees in plastic surgery, adult intensive care and pediatric intensive care will be recruited from the three respective trainee collaborative networks: Reconstructive Surgery Trials Network (RSTN), Trainee Research in Intensive Care (TRIC) and Paediatric Intensive Care Audit Network (PICANet). Trainees from other surgical specialties are also welcome. In order to participate, each site ideally will require at least one surgical and one ICU collaborator to form a “collaborator unit”. From each site, trainees or consultants willing to act as the local lead will be asked to contact the study team to express interest and register their site. The study will be piloted at several sites *a priori* to ensure that accurate and reliable data will be efficiently collected.

Local leads at each site would need to register the audit locally and gain local Caldicott approval. They will receive guidance on local audit registration and approval, as well as on the data collection process. The study will begin in May 2025.

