### Inclusion/Exclusion criteria

All patients who were treated for a severe necrotizing soft tissue infection (including necrotizing fasciitis [ICD-10 M72.6], necrotizing myositis and Fournier’s gangrene [ICD-10 N49.3]) and admitted to ICU (previous 12 months for adult patients, previous 5 years for pediatric patients) are eligible for the study.

Any patients treated solely for cellulitis (non-necrotizing) will be excluded. Patients who were not admitted to ICU will be excluded.

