### Authorship

Collaborator units who submitted all cases over the time period, as confirmed by the consultant lead (either adult, pediatric or both) will be eligible for Pubmed citable collaborator status. They will receive a certificate that demonstrates their contribution to the study, and be Pubmed cited for subsequent publications related to this study. Collaborator units who contributed to data collection but did not reach the threshold will be named under acknowledgments and receive a certificate of participation. Sites will be required to submit a minimum number of cases to be eligible.

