## Strengths and limitations

### Strengths

•First UK multi-centre study of SSTIs, allowing for larger sample size and greater external validity than previous single-centre studies, which are limited by the relatively rarity of SSTIs.•Evaluation of concordance with Sepsis 6/Surviving Sepsis Campaign recommendations in cases of SSTI.•Forms an important baseline in SSTI epidemiology that can be used to standardize future data collection.•Results can be utilized to inform future prospective research

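### The UK epidemiology aim and the baseline claim are broader than an audit of ICU-admitted cases at self-registering hospitals can support

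*Protocol article*

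**What the plan says.** All places are in the protocol article.

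- **Aims**, secondary aim: "To establish epidemiology of SSTIs in the UK". The Materials/patients and methods section then presents the national audit as the means of meeting the listed aims.
- **Strengths**: "Forms an important baseline in SSTI epidemiology that can be used to standardize future data collection".
- **Inclusion/Exclusion criteria**: patients treated for a severe necrotizing infection and "admitted to ICU (previous 12 months for adult patients, previous 5 years for pediatric patients) are eligible for the study". The section adds: "Patients who were not admitted to ICU will be excluded".
- **Materials/patients and methods**, site entry: "trainees or consultants willing to act as the local lead will be asked to contact the study team to express interest and register their site".
- **Authorship**: citable collaborator status goes to "Collaborator units who submitted all cases over the time period, as confirmed by the consultant lead". For other units: "Collaborator units who contributed to data collection but did not reach the threshold will be named under acknowledgments".
- **Data analysis**: descriptive only, using counts, percentages and means with 95% confidence intervals. No rate is mentioned.
- **Limitations**: a single generic line naming selection bias, misclassification bias and missing data. It mentions neither the ICU restriction nor the way sites are recruited.

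**The concern.** The aim and the strength refer to SSTI in the UK as a whole. The design observes a subset defined by three filters: the patient reached ICU, the hospital chose to take part, and the unit submitted the case. The first filter is an explicit eligibility rule, so no supplementary form or analysis plan can reverse it.

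The risk lies in interpretation. If the report keeps the wording of the aim, a description of ICU patients at volunteer hospitals will be read as a description of the disease nationally. Case counts would then be taken as occurrence, and severity and mortality as those of all SSTI. The article intends the results to inform later prospective research, so an over-broad label could carry into feasibility estimates for those studies.

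**Working it through.** The plan states no figure for this point: it has no sample size, no target coverage and no planned rate. The check therefore sets what the aim needs against what the design supplies.

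**1. Occurrence.** To describe how often SSTI occurs in the UK, one needs all cases, or a known fraction of them. The fraction of UK cases that the audit sees is

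f = s × c × k,

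where s is the share of cases admitted to ICU, c is the share of those ICU cases that fall at participating sites, and k is the share of eligible cases that those sites submit.

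- s: not given. The exclusion of non-ICU patients makes s the ceiling for f. With every UK hospital taking part and submitting everything (c = k = 1), f is still s.
- c: not given. Sites register themselves, and the article states no sampling frame or coverage target.
- k: not given. Full submission is a condition of citable status, not of contributing, so k may be below 1.

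An illustration with assumed values shows how little the document fixes f. With k = 1, s from 0.3 to 0.9 and c from 0.25 to 0.75, f runs from 0.3 × 0.25 = 0.075 to 0.9 × 0.75 = 0.675. With s from 0.5 to 0.8 and c from 0.3 to 0.6, it runs from 0.5 × 0.3 = 0.15 to 0.8 × 0.6 = 0.48. None of these inputs comes from the document, so no multiplier for under-counting should be quoted from them.

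**2. Severity mix and mortality.** Let M be mortality among all cases, with M(ICU) and M(non) the values among those admitted and not admitted to ICU. Then

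M = s × M(ICU) + (1 − s) × M(non),

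so M(ICU) − M = (1 − s) × [M(ICU) − M(non)].

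The audit can at best estimate M(ICU), and only for participating sites. The excluded group may include both milder cases and patients who died before reaching ICU. The sign of the bracket is therefore unknown as well as its size. The same reasoning applies to severity at presentation and to management.

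**3. Would a denominator repair the aim?** Total ICU admissions at participating sites would give SSTI per 1,000 ICU admissions. That is a valid quantity, but it describes ICU workload. A catchment population would still leave the non-ICU cases out of the numerator. Neither restores the unqualified aim.

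**4. Time windows.** Adults are collected over 12 months and children over 5 years. Raw adult and paediatric counts cover different periods, in the ratio 1 to 5, and should not be pooled or compared without putting both on an annual basis.

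**5. What the design does support.** The Data collection section lists demographics, presentation, investigations, and surgical and intensive care management. For ICU-admitted patients at participating sites, these can be described directly, and outcome can be too where the data fields record it.

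**The case against.** The strongest reply is that incidence is never promised. Epidemiology can mean who the patients are and how they present and are treated, and the planned analysis contains no rate. This stands: a reader might infer that the report will publish a UK incidence that is too low, but the document does not support that. The mismatch remains on the descriptive reading, because the patients described are ICU patients at volunteer sites and the aim says SSTIs in the UK. The Discussion also ties the lack of epidemiological data to rarity and quotes rates per 100,000, so a reading in terms of occurrence is natural.

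Other points on that side:

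- **Denominator.** A reader might conclude that none is collected. The full field list is in supplementary material that is not shown, and the article is a condensed text, so this cannot be asserted. The point does not depend on it.
- **Baseline sentence.** It goes on to speak of standardizing future data collection, which fits another secondary aim. It is over-broad, not simply wrong.
- **ICU as the natural setting.** The Discussion describes critical care as necessary for patients with SSTI, so ICU cases may be close to the intended population. This could make the gap small, but the explicit exclusion implies that some cases are treated elsewhere, and their share is not given.
- **Existing safeguards.** Selection bias is acknowledged, and the consultant lead confirms completeness for citable units. Both help. Neither tells the reader about the ICU restriction or self-selection as limits on the epidemiological claim.
- **Background figures.** The Introduction says "There are estimated to be 500 new cases every year with 0.4 to 0.53 cases per 100,000 population". A reader might add this as a further error, since 500 cases at those rates imply 500 / 0.53 × 100,000 = 94 million to 500 / 0.4 × 100,000 = 125 million people. The sentence names no country or year, and no design or analysis figure uses it. It is a matter of background wording and no part of this point.

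**Conclusion.** The point holds in a limited form. As worded, the secondary aim and the baseline claim go beyond what the eligibility rule, site recruitment and acceptance of incomplete contributors can support. The data will describe ICU-admitted SSTI at participating hospitals. They will not establish the occurrence, severity mix or mortality of SSTI in the UK, and the Limitations section does not say so.

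This conclusion rests only on printed text and needs no assumption about coverage or ICU share. The size of any under-count, and the direction of any difference in mortality, cannot be obtained from the document. A specific fold-error would be unsupported.

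Severity is moderate to minor. One of three secondary aims is affected, and the primary audit against SSC and Sepsis 6 is untouched. No eligibility rule or planned analysis has to change.

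**What to change.** 1. In Aims, replace the epidemiology aim with: describe presentation, management and outcome of ICU-admitted SSTI at participating UK hospitals. Give the baseline statement in Strengths the same scope.
2. State that no UK population incidence will be claimed.
3. In Limitations, name the ICU restriction and site self-selection, and say that some contributing units may not have submitted all cases.
4. Optional, if the supplementary data fields do not already cover it: ask each site for total ICU and PICU admissions in the relevant window. Report SSTI per 1,000 ICU admissions from sites with confirmed complete case capture, separately for adults (12 months) and children (5 years). Label it an ICU-based rate, not population incidence.

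Items 1 to 3 cost a few lines of text and a narrower claim. Item 4 costs one aggregate number per site and window.

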## Materials/patients and methods

A national, multi-centered audit of NHS hospitals in England, Wales, Scotland and Northern Ireland will be carried out to achieve the above aims. Data collection will be retrospective to understand how documentation for both SSTIs and sepsis varies between sites, and can inform the methodology for later prospective studies. This study will follow a trainee collaborative model. Trainees in plastic surgery, adult intensive care and pediatric intensive care will be recruited from the three respective trainee collaborative networks: Reconstructive Surgery Trials Network (RSTN), Trainee Research in Intensive Care (TRIC) and Paediatric Intensive Care Audit Network (PICANet). Trainees from other surgical specialties are also welcome. In order to participate, each site ideally will require at least one surgical and one ICU collaborator to form a “collaborator unit”. From each site, trainees or consultants willing to act as the local lead will be asked to contact the study team to express interest and register their site. The study will be piloted at several sites *a priori* to ensure that accurate and reliable data will be efficiently collected.

Local leads at each site would need to register the audit locally and gain local Caldicott approval. They will receive guidance on local audit registration and approval, as well as on the data collection process. The study will begin in May 2025.

### Inclusion/Exclusion criteria

All patients who were treated for a severe necrotizing soft tissue infection (including necrotizing fasciitis [ICD-10 M72.6], necrotizing myositis and Fournier’s gangrene [ICD-10 N49.3]) and admitted to ICU (previous 12 months for adult patients, previous 5 years for pediatric patients) are eligible for the study.

Any patients treated solely for cellulitis (non-necrotizing) will be excluded. Patients who were not admitted to ICU will be excluded.

### Data collection

Routinely collected anonymized data will be uploaded onto REDCap, hosted at the Kennedy Institute of Rheumatology, University of Oxford. REDCap is a secure online platform created to store data for research. Each patient is assigned a REDCap ID, and no patient identifiable data will be held centrally.

Collaborators will be asked to keep an excel spreadsheet linking patient ID to their REDCap number to allow data validation checks later on. This spreadsheet should be stored on the local hospital’s secure server according to local IT policies.

Collaborators will be asked for each patient they upload onto REDCap to collect data on patient demographics, clinical presentation, investigations, and management in surgery and intensive care. A full list of required data fields are available in the supplementary material (Supplementary material 1 and 2).

### Data validation

After the data collection period, approximately 5 % of data at each site will be chosen for data validation. The local lead at each site will be asked to validate the selected proportion of the data at their site.

### Data analysis

As this is an exploratory study, no power calculation will be done for sample size. All data collected on REDCap will be exported to a statistical software platform. All captured data will undergo descriptive analysis. Dichotomous, categorical and short ordinal data will be summarized by counts and percentages. Long ordinal and continuous data will be summarized by an appropriate mean with 95 % confidence interval. Anonymized data will be made publicly available once the study is completed and published.

### Authorship

Collaborator units who submitted all cases over the time period, as confirmed by the consultant lead (either adult, pediatric or both) will be eligible for Pubmed citable collaborator status. They will receive a certificate that demonstrates their contribution to the study, and be Pubmed cited for subsequent publications related to this study. Collaborator units who contributed to data collection but did not reach the threshold will be named under acknowledgments and receive a certificate of participation. Sites will be required to submit a minimum number of cases to be eligible.

### Timeline

The study is currently recruiting collaborators. Data collection has begun in June 2025. We anticipate completion of both recruitment and data collection by 30th November 2025. Estimated completion of data analysis is 31st January 2026.

## Discussion

The SENSEI study will audit adherence to SSC and Sepsis 6 guidelines for SSTI patients. The audit findings will inform clinicians on current practices for sepsis management, identifying key areas for improving clinical practice and for future research. Improved awareness of SSTIs may allow clinicians to recognize these infections early. However, awareness may be limited due to their rare incidence, reflected in the lack of epidemiological data.

The World Society of Emergency Surgery (WSES) recently updated their guidelines on skin and soft tissue infections, which incorporates recent adult SSC guidelines.^15^ On the other hand, international guidelines for pediatric patients have not been established as pediatric cases are even rarer than adults, reported to be 0.293 cases per 100,000 population compared to 0.4–0.53 in adults.^16^

While there is a general consensus regarding treatment principles for these infections, there is lack of high-quality evidence^17^ - the rarity of SSTIs means that the mainstay of current research relies on small single-centered studies. A Cochrane review identified three randomized controlled trials (RCTSs) assessed effects of medical treatment for SSTIs, of which all three has high risk of attrition bias, and one was not blinded.^17^ The rare incidence of SSTIs means single-centered studies struggle to gather a large enough population size to generate meaningful results which may be resolved by multi-centered collaboration.^18^ Existing studies also vary greatly in how they measure patient outcomes.^19^ There has been no significant progression in our understanding of SSTIs in recent years. A multi-centered national study can address some of these issues by increasing the sample size and improving external validity. Designing a standardized form for reporting SSTIs allows for comparison between sites and facilitates a prospective cohort study in a national setting.

Since sepsis is present during these infections, current practices in sepsis management can be studied alongside SSTI management. In England and Wales, it was reported that sepsis was the underlying cause of 3770 deaths and a contributing factor for 25,452 deaths.^20^ Worldwide, sepsis is a leading cause of death with 11 million sepsis-related deaths, representing nearly 20 % of all global deaths.^21^ To reduce sepsis mortality and morbidity, the global initiative SSC published guidelines for sepsis management for adult and pediatric populations.^22^^,^^23^ These guidelines may address variations in sepsis management between hospitals.^24^, ^25^, ^26^ Furthermore, a national UK audit on Sepsis 6 care bundle showed that on average most of Sepsis 6 was not achieved within the first hour for the majority of septic patients.^27^ Evaluating management of sepsis in addition to SSTIs would provide an update on clinical practice and compliance with both SSC and Sepsis 6.

SSTIs also have substantial associated healthcare costs which highlight the importance of further study in this area. An Australian study in 2005 found a mean inpatient cost of managing necrotizing fasciitis of 64,517 AUD (£27,050 in the year of publication), not including future outpatient costs such as physical therapy or prosthetics and potential scar or revision surgery.^28^ A significant proportion of this total cost is due to the necessity for patients with SSTI to be managed in a critical care environment due to the presence of sepsis. Although there are no published data regarding predicted costs of ICU management for SSTIs specifically, baseline ICU costs in the UK have been estimated at around £1600,^29^ and median duration of ICU stay for necrotizing 8 days for this type of infection.^30^

To our knowledge, the SENSEI study will be the first UK multi-centered audit for SSTIs for both adult and pediatric populations. Multi-centered studies for SSTI patients exist in other countries but findings may not be transferable to the UK population.^31^, ^32^, ^33^ This study will establish a network of clinicians who will support and recruit patients for future high quality research in SSTIs, as well as providing a surveillance system for monitoring these infections.

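### The aims cover all UK SSTIs, but only ICU-admitted patients are eligible, and the limitations do not name this restriction

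*Protocol article*

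**What the plan says.** **Who enters.** Under Inclusion/Exclusion criteria, patients must have been treated for a necrotizing SSTI "and admitted to ICU (previous 12 months for adult patients, previous 5 years for pediatric patients) are eligible for the study". The rule is repeated as an exclusion: "Patients who were not admitted to ICU will be excluded". Sepsis is not among the criteria.

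**What is claimed.** The primary aim is "To audit current practice for SSTIs against SSC and Sepsis 6 guidelines for adults and children", and one secondary aim is "To establish epidemiology of SSTIs in the UK". Neither mentions intensive care. The Discussion describes an audit of guideline adherence in SSTI patients and a future surveillance system. The Strengths claim better external validity than single-centre work and a baseline for SSTI epidemiology.

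**Why sepsis standards are applied.** The Discussion reasons: "Since sepsis is present during these infections, current practices in sepsis management can be studied alongside SSTI management". The Introduction describes the infections as "characterized by rapidly progressive necrosis of subcutaneous tissue, fascia or muscle, accompanied by sepsis". The Abstract is weaker: "Severe soft tissue infections are surgical emergencies typically accompanied by sepsis".

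**What is admitted as a limitation.** The Limitations list selection bias, misclassification bias and missing data as standard features of retrospective data. The ICU restriction is not named.

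**The concern.** The population that is sampled is narrower than the population in the aims. Patients who recovered without intensive care, and patients who died before reaching it, cannot be entered. No data field or later analysis can bring them back.

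This would matter little if ICU admission were unrelated to the care being audited. The article's own reasoning suggests that it is related. The Introduction says that early debridement lowers the risk of septic shock and multi-organ failure. The Discussion says that SSTI patients need critical care because of sepsis. Taken together, early care can influence who reaches the ICU and so who is counted.

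The second part concerns the standards. Sepsis 6 and the Surviving Sepsis Campaign (SSC) guidelines are for patients with sepsis. If sepsis is typical but not universal, some eligible patients may fall outside them.

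At stake is what the audit may conclude. Followed as written, it would describe practice and epidemiology for UK SSTIs from a sample that supports statements only about ICU-admitted SSTIs.

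**Working it through.** The article states no compliance figure, sample size or power, so there is no figure to reproduce. The check has two parts.

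**1. The sections side by side**

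- Population sampled (Inclusion/Exclusion criteria): necrotizing SSTI and ICU admission.
- Population claimed (Aims, Discussion, Strengths): SSTIs in the UK, adults and children, without an ICU qualifier.
- Disclosure (Limitations): selection bias in general terms only.
- Sepsis: present (Discussion), accompanying (Introduction), typical (Abstract), and not an eligibility criterion.

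The first two do not match, and the third does not bridge them.

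**2. What the mismatch could do to a compliance percentage**

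Every input below is an assumption; the document gives none.

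*Selection on ICU admission.* Let c be compliance among all patients to whom the standard applies, a the probability of ICU admission if compliant, and b the probability if not. Compliance among ICU patients is

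c·a / (c·a + (1 − c)·b).

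| c | a=0.7, b=0.7 | a=0.6, b=0.7 | a=0.5, b=0.7 | a=0.5, b=0.9 | a=0.7, b=0.6 |
|---|---|---|---|---|---|
| 20% | 20.0% | 17.6% | 15.2% | 12.2% | 22.6% |
| 40% | 40.0% | 36.4% | 32.3% | 27.0% | 43.8% |
| 60% | 60.0% | 56.3% | 51.7% | 45.5% | 63.6% |

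For example, c = 0.6, a = 0.5, b = 0.9 gives 0.30 / (0.30 + 0.36) = 45.5%. With a = 0.7 and b = 0.6 it gives 0.42 / (0.42 + 0.24) = 63.6%. The difference vanishes when a = b. It is downward if compliant patients reach ICU less often, and upward if they reach it more often, for instance because sicker patients are treated faster.

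*Patients without sepsis in the denominator.* Let s be their share, q the proportion of them recorded as having the bundle met, and c now compliance among the septic ICU patients. If all are pooled, the reported figure is

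(1 − s)·c + s·q.

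- c = 40%: s = 0.05, q = 0.2 gives 0.38 + 0.01 = 39%; s = 0.20, q = 0 gives 32%.
- c = 60%: s = 0.05, q = 0.2 gives 0.57 + 0.01 = 58%; s = 0.20, q = 0 gives 48%.
- s = 0: no change.

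These figures show only that the effect can be nil, small or material. They are not estimates for this audit.

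**The case against.** The strongest reply is that this is a matter of wording and that nothing has been shown to be miscalculated. Much of that is right.

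- **Denominator.** A reader might infer that compliance will be computed on the wrong denominator. The document does not support this. The article fixes no compliance denominator, time zero or scoring rule: Data analysis promises counts and percentages, and Data collection refers the field list to supplementary material that is not shown. An audit can enrol every ICU case and score each standard only where it applies.
- **Timing.** A reader might also infer that ICU admission always follows a first-hour bundle. The first hour appears only in the account of an earlier audit, which found that "on average most of Sepsis 6 was not achieved within the first hour for the majority of septic patients". The article does not say when ICU admission falls relative to recognition of sepsis, and sepsis could first be recognised in the ICU.
- **Sepsis among ICU patients.** The Discussion ties critical care to sepsis, so ICU admission should make sepsis more likely than in SSTIs at large. The share without sepsis may be small.
- **Mortality.** Conditioning on survival to ICU would affect a mortality result, but the article does not name mortality as an outcome of this audit.
- **Design.** ICU-only eligibility is stated openly and suits a collaboration of surgical and ICU trainees in an exploratory, descriptive audit. With ICU-admitted SSTI as the target, the sample would be sound.

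All of this stands, and it removes any claim that the primary result is biased by a known amount. It leaves the mismatch between the eligibility rule and the unrestricted aims and strengths. A general mention of selection bias does not tell the reader that every non-ICU case was excluded by design.

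**Conclusion.** The concern holds as a mismatch of scope. The eligibility rule supports conclusions about ICU-admitted SSTIs, while the aims and strengths claim UK SSTIs generally. Because ICU admission can depend on early care on the article's own reasoning, compliance and epidemiology in this sample need not carry over to all UK SSTIs. In addition, eligibility has no sepsis criterion and the article's statements on how regularly sepsis occurs differ, so some included patients may fall outside the sepsis standards.

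Neither the size nor the direction of any difference in compliance can be derived from the document. It would be zero if ICU admission were independent of compliance and every included patient were septic. The conclusion on scope rests on no numerical assumption, since it follows from the text alone.

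**What to change.** - Restate the primary aim and the conclusions as concerning ICU-admitted SSTI, and drop or qualify the claim to establish UK SSTI epidemiology.
- Name the ICU restriction in the Limitations, with the reason it matters: admission may depend on the care being audited.
- Report Sepsis 6 and SSC compliance for all included patients and, as a second result, for those who meet one sepsis definition common to all sites. This definition should not rest only on whether sepsis was documented as recognised. The Introduction stresses early misdiagnosis, and a denominator limited to recognised cases would itself select on the practice under audit.
- Optionally, where a site's coding query allows, collect an aggregate count of non-ICU SSTI cases so that the selected fraction is visible.

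The cost is a narrower claim and a little more analysis. The rewording needs no new data. The second result depends on whether the collected fields allow the definition to be applied. The optional count is extra work for sites whose data collection, according to the Timeline, is already under way and due to end on 30 November 2025.
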